## Abstract

**Introduction:**

Timely and accurate identification of stroke subtypes, particularly intracerebral haemorrhage (ICH) and large vessel occlusion (LVO), is essential for improving stroke outcomes. Biomarkers have shown potential in identifying these subtypes. Glial fibrillary acidic protein (GFAP), which is elevated in ICH, and D-dimer, which is associated with LVO, are promising for rapid, point-of-care identification. This study evaluates whether combining GFAP and D-dimer with clinical features improves the diagnostic accuracy for ICH and LVO.

**Methods and analysis:**

This is a multicentre, observational diagnostic accuracy study recruiting a minimum of 257 patients with suspected stroke within 6 hours of symptom onset from two UK hyperacute stroke centres. The study will integrate clinical features and point-of-care biomarker results using the LVOne test (GFAP and D-dimer) to develop diagnostic models that differentiate ICH and LVO from other stroke presentations. Patients will be identified on hospital arrival, and clinical variables and blood samples collected immediately, with the final diagnosis recorded prior to discharge. Statistical analyses will assess discrimination, calibration and clinical utility, with sensitivity, specificity and predictive values reported. Model development and reporting will follow the Transparent Reporting of a Multivariable Prediction Model for Individual Prognosis or Diagnosis+Artificial Intelligence and the Standards for Reporting of Diagnostic Accuracy Studies guidelines.

**Ethics and dissemination:**

The study is registered with ISRCTN (ISRCTN35174477). Ethical approval has been obtained from the Yorkshire & The Humber – Leeds West Research Ethics Committee (25/YH/0102) and the Health Research Authority. Results will be disseminated via open-access peer-reviewed journals, presentations at national and international conferences and summaries for patient and public contributors.

WHAT IS ALREADY KNOWN ON THIS TOPICExisting prehospital tools, such as FAST (Face, Arm, Speech Test), are designed for undifferentiated stroke recognition and are not intended to distinguish intracerebral haemorrhage (ICH) or large vessel occlusion (LVO).Brain-specific biomarkers, such as glial fibrillary acidic protein (GFAP) and D-dimer, have shown promise in differentiating stroke subtypes, but most studies have assessed them in isolation or outside of real-world emergency care pathways.WHAT THIS STUDY ADDSThis multicentre study will evaluate the diagnostic performance of the LVOne test, a point-of-care lateral flow platform measuring GFAP and D-dimer, in combination with routinely available clinical features, in patients with suspected stroke within 6 hours of onset.The study will determine whether integrating GFAP and D-dimer with clinical features into diagnostic models improves diagnostic accuracy for differentiating ICH and LVO.HOW THIS STUDY MIGHT AFFECT RESEARCH, PRACTICE OR POLICYIf the models show adequate performance, they will inform the design of future prehospital validation studies and could ultimately support earlier, more accurate triage of suspected stroke patients.The findings of this study may help refine ambulance destination decisions and prehospital treatment strategies, such as blood pressure lowering in ICH or direct transfer of patients with LVO to thrombectomy-capable centres.

## Introduction

 In the UK, ambulance services commonly use the Face, Arm, Speech Test (FAST) for stroke recognition.^1–3^ However, tools such as FAST were developed to detect undifferentiated stroke and were not intended to identify intracerebral haemorrhage (ICH) and large vessel occlusion (LVO).^4–6^

Among stroke subtypes, ICH and LVO are particularly severe. Timely treatment, such as blood pressure lowering to limit haematoma expansion in ICH or thrombectomy for LVO, is critical^7
8^ and has shifted the focus to the prehospital phase. The Intensive Ambulance-Delivered Blood Pressure Reduction in Hyper-Acute Stroke Trial (INTERACT4) showed that intensive blood pressure lowering initiated in the ambulance significantly reduced death and disability at 90 days in patients later diagnosed with ICH, but worsened outcome in those with ischaemic stroke (IS), including LVO.^9^ The Effect of Direct Transportation to Thrombectomy-Capable Centre vs Local Stroke Centre on Neurological Outcomes in Patients With Suspected Large-Vessel Occlusion Stroke in Nonurban Areas Trial (RACECAT) found that bypassing the nearest stroke centre to transport suspected stroke patients directly to a thrombectomy-capable centre was associated with worse outcomes in patients ultimately diagnosed with ICH.^10^ These findings underscore the importance of distinguishing stroke subtypes in the ambulance to guide appropriate prehospital care and destination decisions.

To realise this ambition, a reliable method that can quickly and accurately differentiate between stroke subtypes in the prehospital setting is required. Although there has been considerable interest in prehospital scales based on clinical features for this purpose,^11–13^ concerns remain regarding their real-world accuracy when used alone.^14^ Recently, innovative technologies, such as brain-specific biomarker testing, have emerged as potentially cost-effective and non-invasive approaches to facilitate early diagnosis and treatment in patients with suspected stroke.^15^ Among these biomarkers, glial fibrillary acidic protein (GFAP), an astrocyte marker that rises early after ICH, and D-dimer, a fibrin degradation product indicative of intravascular coagulation, have shown promise in distinguishing between stroke subtypes.^16
17^

A pooled analysis of 12 studies demonstrated that GFAP could differentiate ICH from IS and stroke mimics, with a sensitivity of 78% (95% CI 67 to 86%) and a specificity of 95% (95% CI 88 to 98%).^16^ Furthermore, a study by Ramos-Pachón *et al*^17^ found that D-dimer was associated with LVO and, when combined with a National Institutes of Health Stroke Scale (NIHSS) score of ≥10, detected LVOs with 35% sensitivity and 93% specificity. These findings suggest that combining GFAP and D-dimer with clinical features could help identify ICH and LVO with sufficient diagnostic accuracy to assist prehospital clinicians in making crucial decisions regarding therapeutic interventions (eg, lowering blood pressure for patients with ICH) and determining appropriate transport destinations.

The aim of this study is to investigate whether diagnostic models based on clinical features combined with point-of-care GFAP and D-dimer tests can accurately determine stroke subtypes in patients with suspected stroke presenting to participating hospitals within 6 hours of symptom onset.

## Study objectives

### Primary objective

To develop and validate diagnostic models that combine clinical features with results from UpFront Diagnostics’ GFAP and D-dimer point-of-care lateral flow tests (collectively referred to as the ‘LVOne test’) to identify ICH and LVO in adults with suspected stroke presenting within 6 hours of symptom onset.

### Secondary objectives

To estimate the diagnostic accuracy of GFAP and D-dimer, individually and in combination, for identifying ICH and LVO.To compare the performance of models based on clinical features alone with models that additionally incorporate LVOne biomarker results.To describe the feasibility and timing of point-of-care biomarker sampling in the early in-hospital phase.

If successful, and if the models demonstrate adequate performance, this work will provide a foundation for future prospective validation studies in the prehospital setting and could ultimately support a shift from generic prehospital stroke recognition towards early differentiation of stroke subtypes, enabling more targeted treatment and triage (eg, direct transport of patients with LVO to thrombectomy-capable centres and prehospital blood pressure lowering in ICH).

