Stroke subtype classification using the LVOne will be performed in accordance with the manufacturer’s LVOne intended use and the prespecified combined clinical-biomarker rule to classify patients into haemorrhagic stroke or LVO. Haemorrhagic stroke will be defined as FAST ≥1 and GFAP positive (intensity ≥1), irrespective of D-dimer. LVO will be defined as FAST ≥2, GFAP negative (intensity=0) and D-dimer positive (intensity ≥2). All other combinations will be classified as non-haemorrhagic and non-LVO. These LVOne stroke subtype classifications will not be performed by clinical staff in real time; instead, they will be derived analytically by the research team in the analysis phase at the end of the study based on the recorded FAST scores and LVOne intensity readings.

An enzyme-linked immunosorbent assay (ELISA) will also be used to quantify GFAP and D-dimer concentrations. Results from the ELISA will be compared with those from the lateral flow assays to assess analytical agreement. If GFAP and D-dimer alone are insufficient to distinguish stroke subtypes with adequate accuracy, additional plasma biomarkers previously shown to differentiate between stroke, stroke mimics, and specific subtypes may also be explored.

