### Sample size

This study aims to ‘rule in’ patients with ICH and LVO; therefore, the sample size calculation prioritises high specificity.

Assuming a 10% prevalence of both ICH and LVO, a sample size of 257 patients with suspected stroke is required, including a minimum of 26 confirmed cases for each subtype. The sample size calculation is based on a diagnostic accuracy framework using the method described by Bujang and Adnan,^24^ in which null and alternative hypotheses are specified for sensitivity and specificity.

Based on our previous work, which demonstrated a specificity of 90% and a sensitivity of 50% for a clinical model with nine predictors,^25^ the current study is powered to detect an improvement to 95% specificity and 80% sensitivity for the detection of ICH and LVO, with 80% power and a significance level of 0.05.^24^

The number of cases contributing to the primary analysis will be monitored throughout the study. If necessary, recruitment may be adjusted to ensure adequate representation of target subtypes.

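### The combined models are compared only with clinical features alone, so beating that comparator does not by itself show that they add to the biomarker strip or to the LVOne rule

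*Protocol article*

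**What the plan says.** The Abstract poses the question as one about combination: "This study evaluates whether combining GFAP and D-dimer with clinical features improves the diagnostic accuracy for ICH and LVO". The protocol then treats the two components of the combination differently.

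- **Clinical features.** The second secondary objective is "To compare the performance of models based on clinical features alone with models that additionally incorporate LVOne biomarker results". This is the only comparison between models that the article states.
- **Biomarkers.** The first secondary objective is "To estimate the diagnostic accuracy of GFAP and D-dimer, individually and in combination, for identifying ICH and LVO". The task is estimation, and the Statistical analysis section gives these analyses their own reporting guideline.
- **The manufacturer's rule.** The section describing the LVOne test fixes a FAST-plus-strip classification. For ICH it reads: "Haemorrhagic stroke will be defined as FAST ≥1 and GFAP positive (intensity ≥1), irrespective of D-dimer". The research team will derive it at the end of the study, but no section sets the new models against it.
- **Sizing.** The null is an earlier nine-predictor clinical model with 50% sensitivity and 90% specificity, and "the current study is powered to detect an improvement to 95% specificity and 80% sensitivity for the detection of ICH and LVO".

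The Introduction cites a pooled analysis of 12 studies in which GFAP separated ICH from ischaemic stroke and mimics with 78% sensitivity (95% CI 67 to 86%) and 95% specificity (95% CI 88 to 98%).

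**The concern.** A combination has two ingredients. To show that combining them helps, it must be compared with each ingredient, and the protocol names only one.

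For ICH the comparator left out may be the stronger of the two. The pooled GFAP sensitivity is 2 points below the study's target and the specificity equals it, whereas the clinical model is 30 and 5 points below. A fitted model that did little more than reproduce the GFAP line could beat clinical features alone and be reported as support for the combination.

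The practical stake is the next step. The protocol makes adequate performance the route to prehospital evaluation. A multivariable model and a one-line rule (FAST plus a visible line) are different things to take into an ambulance, and the planned comparison does not address the choice between them.

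**Working it through.** **Inputs.** From Sample size: null 50%/90%, target 80%/95% (sensitivity/specificity), power 80%, alpha 0.05, prevalence 10%, N = 257, at least 26 cases per subtype. From the Introduction: GFAP 78% (67 to 86%) and 95% (88 to 98%). The article does not state sidedness; two-sided is assumed because it reproduces N.

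**1. The plan's own figure.** One-sample exact binomial test, 0.025 in the upper tail.

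- Specificity, 0.90 against 0.95: the smallest n reaching 80% power is 231 non-cases (reject at ≥217 correct; tail probability 0.0239 under the null; power 0.816). 231/0.9 = 256.7, so N = 257, as stated.
- Cases: 0.10 × 257 = 25.7, so 26, as stated.
- Sensitivity, 0.50 against 0.80, needs only 20 cases (reject at ≥15; power 0.804), or 20/0.1 = 200 patients. Specificity therefore drives N.

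**2. Who clears the same null?** With 26 cases, reject at ≥19 detected (tail probability 0.0145 at 0.50). With 231 non-cases, reject at ≥217 correct. The probability of clearing the null is P(X ≥ 19) with X ~ Bin(26, sensitivity), and P(Y ≥ 217) with Y ~ Bin(231, specificity).

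| True accuracy | Sensitivity test | Specificity test |
|---|---|---|
| Target model, 80%/95% | 0.869 | 0.816 |
| GFAP alone, point estimates 78%/95% | 0.804 | 0.816 |
| GFAP alone, lower CI limits 67%/88% | 0.334 | 0.002 |
| GFAP alone, upper CI limits 86%/98% | 0.978 | 0.9999 |

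In patients, the difference between 80% and 78% sensitivity is 26 × 0.80 − 26 × 0.78 = 20.80 − 20.28 = 0.52 of a case.

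**3. What can a paired comparison deliver?** Near a zero difference, the 95% half-width is 1.96 × √(d/n), where d is the proportion of patients whom the two methods classify differently. The protocol gives no value for d, so these are assumptions.

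- Specificity, n = 231: d = 0.05 gives 1.96 × √(0.05/231) = 2.9 points; d = 0.10 gives 4.1 points.
- Sensitivity, n = 26: d = 0.10 gives 1.96 × √(0.10/26) = 12 points; d = 0.20 gives 17 points.

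**4. Could it be a powered test?** Not for a 2-point sensitivity gain. McNemar sizing, n = (1.96√d + 0.8416√(d − 0.02²))²/0.02², gives 391 ICH cases at d = 0.02 (every disagreement favours the model), 979 at d = 0.05 and 1,960 at d = 0.10. With 26 cases, exact McNemar needs at least a 6–0 split, so even a one-directional 20-point gain has power P(Bin(26, 0.20) ≥ 6) = 0.42.

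**The case against.** **An analysis plan not shown could add the comparison.** It could, and extra contrasts often sit there. But the protocol itself fixes the clinical-only comparator, in an objective and in the sizing null. If the analysis plan already names the other two, all that remains is to align the protocol with it.

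**The text does not contradict itself.** This stands. Adding biomarkers to clinical features is a fair reading of the study question, and it fits the Introduction's doubts about clinical scales used alone. The point is that the comparison is incomplete for the claim, not that it is wrong.

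**A reader might infer that the strip alone already reaches the ICH target.** The documents do not support this. The 78%/95% is a pooled figure, and nothing ties it to this strip at its 213 pg/mL cut-off. Over the cited intervals GFAP alone could clear the null rarely or almost always. The Sample size section also states planning hypotheses, not a declared success criterion.

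**A reader might infer that the study could not tell the model from the strip or the rule at all.** That goes too far. Biomarker accuracy is estimated and the rule is derived in the same cohort, so an informal side-by-side is possible. What is not planned is a paired difference with its interval, specified before results are known.

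**A reader might infer that the study has some 2% power against GFAP alone.** For specificity this is not power: null and alternative are both 95%, so the 2.4% rejection rate of the exact test is type I error.

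**The argument does not carry over to LVO.** Agreed for the near-target argument. The cited D-dimer result, combined with NIHSS ≥10, is 35% sensitivity and 93% specificity, well short of target on sensitivity. The documents give no accuracy for the LVOne rule in either subtype.

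**Conclusion.** The point holds in a limited form. The only stated model comparison and the sizing null are both clinical-only, so beating the clinical model, or meeting 80%/95%, does not by itself show that the combined model adds to the biomarkers or to the LVOne rule. This follows from the choice of comparator and does not depend on how accurate the strip proves to be.

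The size of the problem is illustrated for ICH only. At the pooled point estimates, GFAP alone clears the null about as often as the target model: 80% against 87% for sensitivity, and 82% for both for specificity. This rests on the exact two-sided test that reproduces N = 257, and on pooled estimates that may not transfer to this device; the ranges over their intervals (33–98% and 0.2% to almost 100%) belong with any citation of these figures.

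The planned clinical-only comparison remains valid for its own question. The change is an inexpensive improvement to what the study can conclude.

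**What to change.** Extend the second secondary objective and the Statistical analysis section along these lines:

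*In the same participants, and for ICH and LVO separately, the combined models will also be compared with (a) a biomarker-only model and (b) the prespecified LVOne rule. We will report the difference in AUC (biomarker-only model), and for both comparators the paired differences in sensitivity and specificity at a prespecified model threshold and the difference in net benefit, with the LVOne rule entered as a further strategy on the decision curve. All will carry 95% CIs and be presented as estimates, not powered tests.*

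Two conditions matter:

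- **Optimism.** Correct every fitted-model quantity with the bootstrap already planned, including sensitivity, specificity and net benefit as well as AUC. The rule is fixed in advance while the models are fitted on the same patients, so uncorrected differences would favour the model on exactly this question.
- **Wording of the claim.** Add to Sample size that meeting 80%/95% shows improvement over a clinical model only, and is not evidence of a gain over GFAP or the LVOne rule.

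The cost is protocol wording and a little more analysis on data already being collected, with no added patients or procedures. The downside is wide intervals for sensitivity (about 12–17 points either side, against 3–4 for specificity, under the assumed disagreement) and possibly a more modest claim for the combined model.

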## Study design

DIAGnosis using NOvel technology for Subtypes In Stroke (DIAGNOSIS) is a two-centre prospective diagnostic accuracy study of patients with suspected stroke presenting within 6 hours of symptom onset to two hyperacute stroke centres in Greater Manchester (GM). The diagnostic accuracy of the models will be evaluated against final diagnoses established by CT and/or MRI of the brain.

### Study procedures

Recruitment will take place at two major stroke centres in GM: Salford Royal Hospital and Fairfield General Hospital. At each participating site, a member of the direct clinical care team will approach suspected stroke patients within 6 hours of symptom onset on arrival to conduct initial screening and identification.

If the patient is deemed to meet the eligibility criteria on arrival, a finger-prick capillary blood sample will be immediately collected (within 6 hours of symptom onset) from the patient for the LVOne test. The sample will then be provided to the research team for testing, with the clinical care team remaining blinded to the result to avoid any possible changes to clinical care. A venous blood sample will be collected at the same time for laboratory measurement of GFAP and D-dimer. The sample will be processed as soon as possible but no later than 1 hour after collection.

Once emergency assessments and treatments have been completed, and after all LVOne testing and baseline blood sampling have been performed within the 6 hour onset window, patients will be approached for enrolment and written consent no later than 72 hours after hospital arrival. If the patient has capacity, they will be provided with a participant information sheet and a verbal explanation, and given adequate time to ask questions before written consent is obtained.

Since patients with suspected stroke frequently lack capacity, and assessments must be conducted urgently, it is not always feasible to seek prospective informed consent before LVOne testing and blood sampling. A deferred consent approach will therefore be used in accordance with the UK Mental Capacity Act 2005. Patients who regain capacity within 72 hours of hospital arrival will be approached for written informed consent. For those who remain unable to consent, the opinion of a personal consultee (such as a relative or close friend) will be sought, or, if none is available, the opinion of a nominated (professional) consultee independent of the study team. If neither consent nor the opinion of a consultee is obtained within 72 hours, all study samples and LVOne results for that individual will be destroyed and no further data will be collected.

Routinely collected prehospital and hospital clinical data, as well as discharge diagnosis and treatment information will be extracted from the medical records.

### Justification for emergency consent process

To simulate prehospital conditions and support early diagnostic model development, samples will be collected immediately on hospital arrival, including finger-prick and venous blood samples under an ethically approved deferred consent process. Early sampling is critical, as both clinical features and biomarker levels change rapidly following stroke onset; timely collection ensures scientific validity by capturing the early pathophysiological state. While early clinical data can be retrospectively extracted from medical records after consent, biomarker testing must be performed promptly at presentation.

Finger-prick sampling for the LVOne test is minimally invasive, consistent with routine clinical practice (eg, capillary blood glucose testing), and will be performed by clinical staff who remain blinded to the result. Venous blood samples will be taken alongside routine clinical draws where feasible to avoid additional venepuncture and minimise patient burden. If this is not possible, a separate research sample will be collected as soon as possible by the clinical team following verbal consent. This approach enables timely data collection without delaying urgent clinical care, while maintaining ethical safeguards and patient comfort.

### Justification for hospital-based design

The study was designed as a hospital-based evaluation as an initial step in the clinical validation of the LVOne device. Before implementation in the prehospital setting, it is important to establish the feasibility, diagnostic performance and operational characteristics of the test within a controlled clinical environment, where standard reference diagnostics and clinical oversight are readily available.

Conducting the study in the hospital setting allows for timely blood sampling in the hyperacute phase, close alignment with routine clinical workflows and direct comparison with imaging-based diagnoses. It also enables concurrent collection of venous blood samples for laboratory-based assays, minimising additional procedures and patient burden while facilitating assessment of analytical agreement.

Implementation in the prehospital setting would require additional considerations and substantial resources, including training a large number of ambulance personnel, integration into time-critical emergency workflows and system-level coordination across ambulance services. In addition, individual ambulance clinicians may encounter relatively few eligible stroke cases, meaning that a large number of prehospital providers and sites would be needed to achieve the required sample size within a reasonable timeframe. For these reasons, we chose to evaluate LVOne in a hospital-based setting first. These factors would substantially increase study complexity at this stage and are more appropriately addressed following initial clinical validation.

To approximate the intended use in the prehospital pathway and to reflect the urgency and time-sensitive nature of the prehospital phase, blood sampling and testing will be performed as early as possible following hospital arrival and within 6 hours of symptom onset. If the device and resulting models demonstrate adequate diagnostic performance in this setting, the next stage will be to evaluate LVOne in the prehospital environment, and we will seek funding to support implementation and testing in ambulances and other prehospital services.

